The major outcome of interest of the VIKIPEDIA study is whether oral administration of MK-7 in ESKD patients undergoing PD can slow progression of arterial stiffness. We expect that MK-7 supplementation will enhance MGP carboxylation and phosphorylation, suppress circulating dp-ucMGP, slower progression of arterial stiffness [assessed by PWV increase] and thus ameliorate CV disease. Further research questions will be whether treatment with MK-7 might reduce all-cause and CV mortality and improve 24-hour ambulatory BP. Our research hypothesis is that daily, high dosage of MK-7 supplementation might increase γ-carboxylation and thus activation of MGP, decrease circulating dp-ucMGP and thus ameliorate CV disease in the PD population. Moreover, we will assess cross-sectional information regarding the prevalence of arterial stiffness and vitamin K deficiency in PD patients, along with prospective data on the development of arterial stiffness in PD patients in the control group (not treated with MK-7).

1. **Materials and Methods**

*Trial Design and Setting*

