Brachial and central aortic BP, AIx and PWV will be recorded under ambulatory conditions over 24 hours with the brachial cuff-based oscillometric device Mobil-O-Graph (IEM, Stolberg, Germany) (28). The BP-detection unit of this device was validated according to the criteria of European Society of Hypertension/European Society of Cardiology (ESH/ESC). The monitor is programmed to measure BP 3 times per hour during daytime (07:00 to 22:59) and 2 times per hour during nighttime (23:00 to 06:59). ABPM will be considered complete when >80% of readings will be valid with ≤2 non-consecutive daytime hours with <2 valid recordings and ≤1 nighttime hour without valid recording. Participants with incomplete or invalid recordings will be asked to repeat ABPM within the next week.

The methodology incorporated by the Mobil-O-Graph device is described in detail elsewhere (29). After the oscillometric recording of brachial BP, the cuff re-inflates at the diastolic phase, acquiring the brachial pressure waveforms for ~10 seconds with a high-fidelity pressure sensor (MPX5050, Freescale, Tempe, AZ, USA). Subsequently, the software (HMS version 4.5) regenerates the aortic pulse waveform by means of an ARCSolver algorithm using a generalized transfer function. The calculation of central aortic pressures was based on the C1 (brachial systolic BP /diastolic BP) calibration method. The Mobil-O-Graph device performs also wave separation analysis by decomposing the aortic pulse waveform into forward- and backward-traveling pulse waves with a triangular aortic flow waveform (27). Utilizing parameters from pulse wave and wave separation analyses, the ARCSolver algorithm estimates the following indices:

1. augmentation pressure, defined as the difference of the pressure at second minus the pressure at first inflection point of the systolic phase of pulse wave;
2. AIx, an index of pulse wave reflection at the level of microcirculation, defined as the ratio of augmentation pressure to aortic PP;
3. PWV, a direct marker of arterial stiffness, calculated from the reconstructed aortic pulse waveform via mathematical algorithms, taking into account the characteristic impedance and age and assuming a three-element Windkessel model.

*Study endpoints*

We will consider two primary endpoints:

-Progression of aortic stiffness, assessed by the absolute change in the value of PWV after 1.5 years of treatment compared to PWV at baseline before the initiation of treatment.

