-The occurrence of non-fatal CV events, including acute myocardial infarction, acute coronary syndrome, embolism, peripheral arterial disease and stroke.

We will consider the following secondary endpoints:

-All-cause and CV mortality

- The absolute change from baseline in the values of PWV indices, wave reflection indices, heart-rate-adjusted augmentation index, SVRI and PP

-The percentage change over time in the values of PWV indices, wave reflection indices, heart-rate-adjusted augmentation index SVRI and PP

-PD adequacy (RRF preservation, Kt/V)

- Rate of infections and peritonitis

-The absolute change in 24 hour ambulatory BP indexes and aortic systolic BP

-Changes in serum parathormone from baseline

-Changes in the calcium phosphorus product from baseline

- Fracture incidence

- Incidence of joint/muscle pain

*Statistical analysis*

All eligible patients who provided informed consent will be enrolled and randomized to the treatment or placebo group (on a 1:1 ratio), stratified by sex, age and center. All details will be described in a statistical randomization report that will be kept concealed and will be opened only after the enrollment will be completed.

One of the primary endpoints is progression of arterial stiffness, defined as the absolute change in PWV value at the end of the 18 months versus the baseline. We hypothesize that the progression – increase of PWV will be lower in the treatment group (20% lower). Therefore, this endpoint will be the PWV increase for every patient (expressed as absolute value and as percentage change over time). To investigate the possible effect of MK-7 supplementation on the other primary endpoint (CV events) Kaplan-Meier curves and Cox regression analysis will be performed.

*Sample size calculation*

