We performed two separate power calculations for our two separate, primary endpoints. The only published study so far assessing dp-ucMGP and clinical hard end-points in PD patients, showed that after a median follow-up of 31 months, a significantly higher incidence of fatal/non-fatal CV events occurred in the patients with high dp-ucMGP levels (64.6% versus 39%). Until to-date no RCTs have been conducted in PD patients, therefore our calculation will be based on already published data in similar populations. We consider that a 28% difference in the incidence of CV events among arms is a significant treatment effect and we expect that the incidence of CV events would be 56% in the placebo and 28% in the treatment group, during the 18 month follow-up. Therefore, with a two-sided significance level of 5%, t-test and 80% power, 96 participants will be required. Accounting for a drop-out of 20%, we will enroll 120 patients (60 in each arm).

For the primary outcome of arterial stiffness progression we performed a separate power analysis. Based on previous studies, we expect that the increase in PWV value (absolute difference from baseline to the end of the study) will be 3 m/s after 1.5 year at the placebo group with an assumed standard deviation of 0.90 m/s (3, 30, 31) and we consider that an absolute difference of 20% in PWV increase among groups, is a significant treatment effect (32, 33). Accounting for an estimating drop-out rate of 20%, with a two-sided significance level of 5%, t-test and 80% power, 120 patients will be required (60 in each group) to detect a significant treatment difference.

*Monitoring*

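### Two separate primary endpoints are each sized at the full two-sided 5% with no rule joining them; if either can carry the trial, the family-wise error is about 9.75%

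*Protocol*

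**What the plan says.** Under Study endpoints the protocol writes "We will consider two primary endpoints". The first is the absolute change in PWV from baseline to 18 months; the second is the occurrence of non-fatal CV events. The Sample size calculation section repeats the separation: "We performed two separate power calculations for our two separate, primary endpoints".

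Each calculation uses the whole 5%:

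- CV events: "we expect that the incidence of CV events would be 56% in the placebo and 28% in the treatment group", and "with a two-sided significance level of 5%, t-test and 80% power, 96 participants will be required". Then "Accounting for a drop-out of 20%, we will enroll 120 patients (60 in each arm".
- PWV, after the 20% drop-out allowance: "with a two-sided significance level of 5%, t-test and 80% power, 120 patients will be required (60 in each group".

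Two other places bear on the point. The Objectives single out arterial stiffness: "The major outcome of interest of the VIKIPEDIA study is whether oral administration of MK-7" can slow its progression. The Statistical analysis section first repeats the absolute-change definition of the PWV endpoint, then adds that "this endpoint will be the PWV increase for every patient (expressed as absolute value and as percentage change over time". Percentage change in PWV indices also stands in the list of secondary endpoints.

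Nowhere does the protocol give a testing order, a division of alpha, an adjustment for two tests, or a statement of what makes the trial positive.

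**The concern.** With two primary endpoints there are two chances of a significant result when the supplement does nothing. Unless a rule links the tests, a reader of the eventual report cannot tell whether one significant endpoint out of two is a positive trial, and the 5% attached to each test does not describe the risk of a false primary claim for the trial as a whole.

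The two expressions of the PWV endpoint add a smaller ambiguity: the version that decides the primary question is fixed in one section and loosened in another.

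The choice of rule also bears on power. The CV-event sample size was worked out with all of the 5%, so some ways of controlling the error would leave that endpoint short of its stated 80%.

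**Working it through.** **1. Reproduce the CV-event sample size.** Inputs from the Sample size calculation section: 56% versus 28%, two-sided 5%, 80% power, 1:1 allocation, 20% drop-out. The text names a t-test; the usual two-proportion formula with pooled variance and no continuity correction is used here.

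n per arm = [z(0.975)·√(2p̄(1−p̄)) + z(0.80)·√(p₁(1−p₁)+p₂(1−p₂))]² / (p₁−p₂)², with p̄ = 0.42

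= [1.960·√0.4872 + 0.842·√0.448]² / 0.0784 = 47.6, so 48 per arm and 96 in all. 96/0.8 = 120.

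This matches the protocol. Power at 48 per arm is 80.4%. At two-sided 2.5% the same formula gives 57.7, so 58 per arm, 116 evaluable and 116/0.8 = 145 enrolled. The stated 96 therefore uses the full 5%.

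**2. Family-wise error if either endpoint suffices.** For independent tests: 1 − 0.95² = 0.0975. For correlated test statistics (bivariate normal, both two-sided at 5%):

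| Correlation | Chance of at least one false positive |
|---|---|
| 0 | 9.75% |
| 0.2 | 9.6% |
| 0.3 | 9.5% |
| 0.5 | 9.1% |
| 0.7 | 8.3% |
| 0.9 | 7.0% |

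The upper bound is 5% + 5% = 10%. The protocol does not give the correlation, so the range is shown.

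**3. Power of each endpoint at 48 evaluable per arm (60 × 0.8).** For PWV, the 20% is read as 20% of the 3 m/s placebo increase: 0.20 × 3 = 0.6 m/s, with SD 0.90, so a standardised difference of 0.667.

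| | at 5% | at 2.5% |
|---|---|---|
| PWV (t-test) | 89.8% | 83.7% |
| CV events (two proportions) | 80.4% | 71.3% |

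On these inputs 80% power for PWV needs only 37 per arm, 74 evaluable, so the PWV figure of 120 does not follow from them. That is a separate matter; here it only explains why PWV power exceeds 80%.

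**4. Power under rules that hold the family-wise error at 5% (independence assumed for the products).**

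- Fixed sequence, PWV then CV events, each at 5%: PWV 89.8%; CV events 0.898 × 0.804 = 72%.
- Holm: an endpoint succeeds if its p ≤ 0.025, or if its p ≤ 0.05 and the other's p ≤ 0.025.
  - PWV: 0.837 + (0.898 − 0.837) × 0.713 = 88%.
  - CV events: 0.713 + (0.804 − 0.713) × 0.837 = 79%.
- Equal split at 2.5% each: PWV 83.7%; CV events 71.3%. Family-wise error 1 − 0.975² = 4.94%.
- Both must succeed: no inflation. Joint power is 0.8 × 0.8 = 64% at the stated powers, or 0.898 × 0.804 = 72% at the recomputed ones.

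**The case against.** The strongest reply is that the analysis plan is not shown and testing order is often written there. A fixed sequence or a both-must-succeed rule would still test each endpoint at 5%, so sizing each at 5% does not by itself rule out a sound design. This stands in part: sizing at 5% excludes only a pre-planned alpha split at the stated power. But the protocol goes further than silence. It calls the endpoints separate, makes both primary, sizes each alone at the full level, and reports no power for any combined rule. The power available for CV events depends on the rule chosen, so the rule belongs beside the sample size.

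A second reply is that the Abstract joins PWV change and CV events under a singular primary endpoint, which could mean that both must succeed. If so, there is no inflation. The hint is weak. Study endpoints and the sample size section both count two, Statistical analysis treats each as one of two, and no joint power is given.

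A third reply concerns the percentage expression, which may be no more than a reporting format: absolute change is the definition in two sections and the basis of the sample size. That is fair. A reader might infer a full third chance of significance, but the two expressions of the same measurement would be expected to correlate strongly and the added error has not been quantified. The inconsistency remains and is easily tidied.

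**Conclusion.** The point holds in conditional form. The protocol names two separate primary endpoints, each at two-sided 5%, without a multiplicity rule or a requirement that both succeed. If either one suffices, the family-wise error is 9.75% under independence, 9.5% at a correlation of 0.3, 9.1% at 0.5, and never above 10%. The either-or rule is an assumption: the protocol states no success criterion at all.

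Three stronger readings are not supported:

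- A reader might infer that the protocol promises a trial-wise 5% and breaks it. The 5% appears only inside each power calculation, as a per-test level.
- A reader might infer that CV events have little power anyway, so demoting them costs nothing. On the protocol's own rates the power is 80.4% at 48 evaluable per arm.
- A reader might infer that a fixed sequence is the only remedy and is free. It is one of several, and it takes confirmatory CV-event power from about 80% to about 72%.

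All power figures rest on the protocol's assumed effects, a comparison of proportions for CV events (the planned analysis is Kaplan-Meier and Cox regression), and independence of the two tests.

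**What to change.** State one decision rule, before any unblinded comparison, that holds the family-wise error at two-sided 5% with 120 patients, and restate the power it gives. Two options suit the document:

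- **(a) Fixed sequence**, in line with the Objectives. Test absolute PWV change first at 5%; test CV events confirmatorily at 5% only if PWV is significant, otherwise report them descriptively. Power is about 90% for PWV and 72% for CV events.
- **(b) Holm's procedure**, which keeps the two endpoints on an equal footing. Power is about 88% for PWV and 79% for CV events.

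If both endpoints are meant to be required, say so and give the joint power instead.

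In the Statistical analysis section, confine the primary PWV endpoint to absolute change and leave percentage change in the secondary list, where it already stands. Make the Abstract's description of the primary endpoint agree.

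The cost is a few sentences, with no change to patient numbers, visits or data collection. The statistical price is modest: some confirmatory power for CV events, larger under (a) than (b), and under (a) no confirmatory CV claim if PWV fails, which places a clinical endpoint behind a surrogate.

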**Acknowledgments**

The VIKIPEDIA researchers would like to thank Nattopharma ASA, Hovik, Norway for supporting our study and providing the MK-7 supplements.

**Table 1.** Inclusion and exclusion criteria of the VIKIPEDIA study.

| **Inclusion and exclusion criteria** | |
| --- | --- |
| Inclusion criteria | Exclusion criteria |
| Age ≥ 18 years | Use of vitamin K antagonist or vitamin K supplements during the past 3 months |
| At least 3 months on PD | Liver disease |
| Life expectancy of ≥ 18 months | Drug or alcohol abuse |
|  | Ongoing malignancy or severe inflammatory disease diagnosis |
|  | Diagnosis of severe gut-disease (inflammatory or short bowel disease) or gastrointestinal malabsorption |
|  | Mental disorder rendering the patient unable to conform with the instructions and fully understand the nature, aim and possible side-effects of the supplementation |
|  | Treatment with phosphate binders (sevelamer) |
|  | Pregnancy or breast-feeding |

**Figure 1.** Design and flow-chart of the VIKIPEDIA trial.

[figure not shown]

